***Confidential***

# Abbreviations

| 6-MWT | 6-Minutes-Walk-Test |
| --- | --- |
| GCP | Good Clinical Practice |
| MLHF Q | Minnesota Living With Heart Failure Questionnaire |
| MR | mitral regurgitation |
| PMVR | Percutaneous mitral valve repair |
| QoL | Quality of life |
| TEE | Trans-esophageal echocardiography |
| TTE | Trans-thoracic echocardiography |

| **Title of Study** | **Safety and efficacy of percutaneous mitral valve repair using the MitraClip® system in patients with diabetes mellitus – The MitraClip® Registry** |
| --- | --- |
| **Principal Investigator** | Univ.- [name], MD |
| **Sub-Investigators** | [name]  [name], MD  [name]  [name]  [name] |
| **Participating Scientists** | [name], B.Sc., M.A. |
| **Study Duration** | First patient in: Q1 2013  Recruitment Phase: 12 months Observational period per patient: 3 months  Last patient out: Q2 2014 |
| **Legal Aspects** | The study will be performed in accordance with the Declaration of Helsinki and the Good clinical practice (GCP)-guideline. |
| **Background** | Mitral valve regurgitation (MR) is the second common valvular heart disease. Percutaneous mitral valve repair (PMVR) with the MitraClip® system is an effective therapeutic alternative for patients who cannot undergo surgery due to high surgical risk. Patients with diabetes mellitus show a negative outcome in percutaneous coronary intervention, aortic valve replacement and cardiac surgery. The impact of diabetes on treatment of MR using the MitraClip® system is not known. Therefore the aim of this observational study is to assess percutaneous mitral valve repair with the MitraClip® system is safe and effective in patients with diabetes mellitus. |
| **Risk-Benefit-Assessment** | All patients will be discussed in the institutional heart team and declined for surgical treatment due to high operative risk. Percutaneous mitral valve repair (PMVR) with the MitraClip® system is an effective therapeutic alternative for patients who cannot undergo surgery due to high surgical risk. Only patient with symptomatic severe or moderate-to-severe MR referred to PMVR with the MitraClip® system will be included in this observational study. |
| **Objectives** | The aim of the study is assess the safety and efficacy of percutaneous mitral valve repair with the MitraClip® system in patients with diabetes mellitus.  **Primary outcome:** The primary endpoint is related to safety with regard to successful MitraClip® implantation, in-hospital complication rate, and 30-day mortality.  **Secondary outcomes:** The secondary endpoints are related to efficacy with regard to procedure duration and radiation time. Further secondary endpoints are changes in MR and clinical parameters: NYHA class, Quality of life, 6-Minutes-Walk-Test (6-MWT), left ventricular ejection fraction, left ventricular end-diastolic diameter. |
| **Study Design** | non-interventional, open-label, mono-center, observational study |
| **Inclusion Criteria** | - Male and female patients aged > 18 years - Patients with symptomatic severe or moderate-to-severe MR undergo PMVR with the MitraClip® system - Group 1: patients with type II diabetes mellitus (oral medication or on insulin therapy) - Group 2: non-diabetic patients - Written informed consent |
| **Exclusion Criteria** | - Patients unwilling or unable to give informed consent - Underage persons |
| **Number of Patients** | All patients with symptomatic severe or moderate-to-severe MR with or without diabetes mellitus type II who will undergo a PMVR with the MitraClip® System at the Heart Center Duesseldorf will be asked to participate in this observational study. The recruitment period will be 12 months. |
| **Intervention** | All included patients with symptomatic severe or moderate-to-severe MR evaluated by trans-thoracic and trans-esophageal echocardiography will undergo PMVR with the MitraClip® System at the Heart Center Duesseldorf according to local standard. The MitraClip® procedure will be performed either in general anesthesia or deep sedation using TEE and fluoroscopy for guidance. |
| **Methods** | After patients given their written informed consent the following data will be collected:   - Demographics and medical history - physical examination and vital signs - medical imaging - periprocedural in hospital data, e.g. procedure duration and radiation time - laboratory parameters (blood samples for biochemistry and hematology analysis) - Trans-thoracic echocardiography (TTE) - Trans-esophageal echocardiography (TEE) - quality of life measured by the Minnesota Living With Heart Failure Questionnaire (MLHF Q)   One follow-up visit will be performed routinely after 3 months. The following outcome parameters will be collected:   - physical examination and vital signs - medical history - NYHA classification - 6-MWT - quality of life measured by the Minnesota Living With Heart Failure Questionnaire (MLHF Q) - Trans-thoracic echocardiography (TTE) - laboratory parameters (blood samples for biochemistry and hematology analysis) |
| **Data Documentation** | All data to be collected will directly be entered into a suitable data base. |
| **Sample Size** | No sample size calculation will be performed because this is an observational pilot study. |
| **Analysis and Statistics** | Continuous data will be expressed as mean ± standard deviation (SD) and compared with the unpaired student`s t-test or Mann-Whitney U test if not normally distributed. Normality will be checked with the Kolmogorov-Smirnov test. Categorical variables will be evaluated as percentage and compared with the qui-square test or Fisher`s exact test. Statistical analysis will be performed with SPSS® Statistics 22 (IBM®) and Prism® (GraphPad®). A p-value <0.05 is considered to be significant. |
| **Ethics and Quality Assurance** | The study will be approved by the local ethics committee. The study will be conducted according to the ICH-GCP criteria of ”Good Clinical Practice“. It will be performed according to the legal data protection requirements. The pseudonymized data will be archived for 5 years at the University Hospital Duesseldorf. Data analysis will be performed pseudonymized. Data protocol and publication will be anonymized. The patients have the right to receive information. |
| **Insurance** | No patients’ insurance is necessary because this is an observational trial. The patients will be treated within the standard therapy for symptomatic severe or moderate to-severe MR. |

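### Diabetic and non-diabetic patients are compared only with unadjusted two-sample tests, so differences in baseline risk can be mistaken for an impact of diabetes

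*Protocol*

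**What the plan says.** The Study Design row of the protocol synopsis describes a "non-interventional, open-label, mono-center, observational study". Under Number of Patients, everyone treated with the device at the one centre "will be asked to participate in this observational study". The Inclusion Criteria then split them by existing disease: Group 1 has type II diabetes on oral medication or insulin, and the comparator is "Group 2: non-diabetic patients". No randomisation, matching or restriction is stated.

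The Background gives the gap the study responds to: "The impact of diabetes on treatment of MR using the MitraClip® system is not known". The Objectives row gives the formal aim as the "safety and efficacy of percutaneous mitral valve repair with the MitraClip® system in patients with diabetes mellitus". The primary endpoint is "successful MitraClip® implantation, in-hospital complication rate, and 30-day mortality".

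Analysis and Statistics fixes the comparisons. Continuous data are "compared with the unpaired student`s t-test or Mann-Whitney U test if not normally distributed", categorical data are tested by chi-square or Fisher's exact test, and the significance threshold is 0.05. The protocol names no regression model, stratification, propensity score or list of confounders. The Sample Size row waives a calculation because this is a pilot.

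**The concern.** Diabetes status is a patient characteristic that nobody assigned. The two groups can therefore differ in age, sex, ventricular function and comorbidity, and these can affect complications, death, walking distance and quality of life. A two-sample test without covariates combines any such difference with whatever diabetes itself contributes.

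The error can go either way. Higher baseline risk in the diabetic group could look like harm from diabetes. A younger diabetic group could hide a real disadvantage and give false reassurance about safety. In both cases the 5% threshold no longer measures the chance of wrongly declaring a diabetes effect. More patients do not help, because the bias stays the same while the standard error shrinks.

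**Working it through.** The protocol states no sample size, group ratio, event rate or effect size, so there is no figure of its own to reproduce. Everything below is illustration on assumed inputs.

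**Inputs from the protocol.** Two non-randomised groups (Inclusion Criteria), unadjusted two-sample tests and a threshold of 0.05 (Analysis and Statistics). Sidedness is not stated; two-sided is assumed.

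**Inputs assumed.** Group sizes n1 (diabetic) and n2 (non-diabetic); one baseline covariate whose mean differs by d SD between the groups; correlation r of that covariate with the outcome; no true effect of diabetes.

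**Continuous outcome.** Spurious difference = r × d, in SD units. SE = √(1/n1 + 1/n2). With m = r × d / SE, the chance of p<0.05 is Φ(m − 1.96) + Φ(−m − 1.96).

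For 30 and 60 patients, SE = √(1/30 + 1/60) = 0.224.

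- d = 0.3, r = 0.3: shift 0.09, m = 0.40, chance 6.9%.
- d = 0.5, r = 0.3, or d = 0.3, r = 0.5: shift 0.15, m = 0.67, chance 10.3%.
- d = 0.5, r = 0.5: shift 0.25, m = 1.12, chance 20.1%.

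Over the same range of d and r, other assumed sizes give:

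| Diabetic / non-diabetic | Lowest | Highest |
|---|---|---|
| 20 / 40 | 6.2% | 15.0% |
| 30 / 60 | 6.9% | 20.1% |
| 50 / 100 | 8.1% | 30.3% |

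**Check by simulation** (4,000 runs per case, no diabetes effect). The t-test is compared with a linear model that adjusts for the imbalanced covariate. The simulation error near 5% is √(0.05 × 0.95 / 4000) = 0.3 percentage points.

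| Sizes, d, r | t-test | Adjusted model |
|---|---|---|
| 30 / 60, 0, 0.5 | 4.7% | 4.8% |
| 30 / 60, 0.5, 0.3 | 10.3% | 5.3% |
| 30 / 60, 0.5, 0.5 | 20.1% | 5.4% |
| 50 / 100, 0.5, 0.5 | 30.0% | 5.1% |

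The adjusted model returns to 5% because the only imbalanced covariate is measured and in the model. That is the best case.

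**Binary outcome.** The primary components are binary, so the continuous figures do not carry over to them. Suppose a risk factor is present in 60% of one group and 40% of the other, with event risk 20% with it and 10% without. The crude risks are 0.6 × 0.20 + 0.4 × 0.10 = 0.16 and 0.4 × 0.20 + 0.6 × 0.10 = 0.14. The crude odds ratio is (0.16/0.84)/(0.14/0.86) = 1.17 with no diabetes effect. With prevalences of 70% and 40% and risks of 30% and 10%, the crude risks are 0.24 and 0.18 and the odds ratio is (0.24/0.76)/(0.18/0.82) = 1.44. These show distortion of the estimate. They are not rejection rates.

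**The case against.** Four objections deserve an answer.

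- *The formal aim is narrower.* Objectives and title ask about safety and efficacy in patients with diabetes. Rates and changes within Group 1 answer that without adjustment, with Group 2 as a crude benchmark. This stands, so it would be wrong to say that the planned analysis cannot meet the study's aim. It does not explain the significance tests between groups or the Background's question about the impact of diabetes.
- *It is a pilot.* Purely descriptive comparison would be defensible in a pilot if labelled so. But the protocol invokes pilot status only to waive the sample size calculation, and sets its 0.05 threshold without any such label.
- *A statistical analysis plan may add adjusted models.* It may, and the absence of a covariate list alone would be no fault in a protocol. Here, however, the protocol itself chooses the between-group tests, the normality check, the software and the threshold, and refers to no further plan.
- *The figures are assumed, and the low end is close to 5%.* Both are true. They show a possibility, not an expected error rate.

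A reader might also infer that differences will be reported as caused by diabetes. No section says so. The documents support only that the differences can be mistaken for such an effect.

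**Conclusion.** The point holds in a limited form. The groups are not randomised and every between-group test named is unadjusted. Followed as written, the plan can give a confounded answer to the question in the Background.

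On the assumed 30 and 60 patients, imbalance of 0.3 to 0.5 SD and correlation of 0.3 to 0.5, the false-positive chance for a continuous outcome is about 7% to 20%. It would be wrong to read 20% as this study's error rate: it is the upper corner of a range in which group sizes, imbalance and correlation are all assumptions. Nor do the documents show that the groups do differ at baseline or in which direction. For the binary primary components, only the distortion of the odds ratio is illustrated.

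This is a cheap improvement that should be made. It is not a defect that invalidates the study.

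**What to change.** Amend Analysis and Statistics before outcomes are compared by group:

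- Keep the crude tests as descriptive, and state that their p-values do not estimate the effect of diabetes.
- Base any statement about the impact of diabetes on a prespecified adjusted between-group estimate with a 95% confidence interval.
- For change in 6-MWT, quality of life, ejection fraction and end-diastolic diameter, use a linear model with group, the baseline value of the outcome, age and sex.
- For implantation success, in-hospital complications and 30-day mortality, use a sparse penalised logistic model with group, age and sex, or group and a single propensity score. Call it exploratory if events are few. Confirm that the method is available in the named software, or name other software.
- Put variables that may be consequences of diabetes only in a sensitivity model, since adjusting for them could remove part of the effect sought. These are GFR, baseline ejection fraction where it is not the outcome, and MR aetiology if recorded. The protocol does not name aetiology as a recorded variable.

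The main models need no new data: demographics are collected at baseline (Methods), and Table 1 schedules the 6-MWT, quality of life and TTE at V1. The cost is a few degrees of freedom and a slightly longer report. Adjustment removes only measured confounding, and age and sex alone will leave some behind; the report should say so.

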**Study Flow Chart**

Table 1: Visit Schedule

| **Procedure** | **Screening/Baseline Visit**  **V1** | **Procedure**  **V2** | **Follow-up Visit**  **V3**  **(after 3 month)** |
| --- | --- | --- | --- |
| Informed Consent | X |  |  |
| In-/Exclusion Criteria | X |  |  |
| Physical Examination | X |  | X |
| Medical History | X |  | X |
| Vital Signs | X |  | X |
| NYHA classification | X |  | X |
| 6-MWT | X |  | X |
| QoL | X |  | X |
| TTE | X |  | X |
| TEE | X | X |  |
| periprocedural data (e.g. procedure time, radiation time) |  | X |  |
| Laboratory analysis* | X |  | X |
| Adverse event assessment |  | X | X |

* Nt-pro BNP, GFR, Creatinine, Urea, hs C-reactive Protein, Procalcitonin, blood count, blood glucose, HbA1c

This clinical investigation plan was subject to critical review and has been approved by the following:

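### Continuous data are summarised as mean ± SD even when Mann-Whitney is used, and a Kolmogorov-Smirnov pre-test chooses between that test and a pooled-variance t-test (minor; secondary and descriptive variables only)

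*Protocol*

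**What the plan says.** The rule stands in the protocol synopsis under Analysis and Statistics. The summary is fixed without exception: "Continuous data will be expressed as mean ± standard deviation (SD"). The same data are then to be "compared with the unpaired student`s t-test or Mann-Whitney U test if not normally distributed", and the switch is decided as follows: "Normality will be checked with the Kolmogorov-Smirnov test". Significance is set by "A p-value <0.05 is considered to be significant".

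The entry names two software packages. It does not say at what level normality is tested, whether the critical values allow for an estimated mean and SD, or whether each group or the combined sample is tested. It offers no unequal-variance form of the t-test and no alternative to mean ± SD.

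The groups are set out under Inclusion Criteria: "Group 1: patients with type II diabetes mellitus (oral medication or on insulin therapy) - Group 2: non-diabetic patients". Their sizes depend on who presents and consents during 12 months of recruitment. Under Sample Size the protocol says "No sample size calculation will be performed because this is an observational pilot study".

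Under Objectives, the continuous secondary endpoints include procedure duration and radiation time. The laboratory footnote to the visit schedule (Table 1) lists "Nt-pro BNP, GFR, Creatinine, Urea, hs C-reactive Protein, Procalcitonin" among other values.

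**The concern.** Three features of the rule deserve a second look.

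1. **Summary and test disagree.** Once a variable has been judged non-normal and sent to a rank test, a mean and SD no longer describe what was compared. For a positive, right-skewed variable they also describe it poorly. Procedure duration, radiation time and NT-proBNP are plausible candidates, although the protocol gives no distributions.
2. **The gate may not do its job.** The Kolmogorov-Smirnov test with mean and SD estimated from the same data has little power unless its critical values are corrected, and the protocol does not say which version applies. The t-test and Mann-Whitney also address different hypotheses, so the data decide which question is answered.
3. **Variances are left unprotected.** A normality test does not look at equality of variance. Student's t-test pools the variances, and that matters when group sizes and variances both differ.

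At stake are the description and the p-values of the continuous secondary endpoints and the laboratory variables.

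**Working it through.** The protocol gives no SD, group size or error rate other than 0.05, so there is no figure of its own to reproduce. Group sizes, SD ratios and distributions below are assumptions, and tests are taken as two-sided.

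**Step 1. Mean ± SD on skewed data.** For a lognormal with median 1 and log-SD s, the mean is exp(s²/2) and the SD is mean × √(exp(s²) − 1).

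| s | Mean | SD | Mean − SD |
|---|---|---|---|
| 0.5 | 1.13 | 0.60 | 0.53 |
| 0.8 | 1.38 | 1.30 | 0.07 |
| 1.0 | 1.65 | 2.16 | −0.51 |

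At s = 1.0 the reported interval runs below zero for a quantity that cannot be negative. Median (IQR) for the same variable is 1 (0.51 to 1.96), from exp(±0.6745 × 1.0).

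**Step 2. Power of the pre-test.** Share of single samples flagged at the 5% level, by simulation with mean and SD estimated:

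| Distribution | n | Uncorrected | Lilliefors-corrected |
|---|---|---|---|
| Exponential | 30 | about 11% | about 80% |
| Lognormal, s = 0.5 | 30 | about 3.5% | about 48% |
| Exponential | 20 | about 4% | not needed here |
| Lognormal, s = 0.5 | 20 | about 2% | not needed here |

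Which column applies cannot be told from the protocol.

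**Step 3. Pooled t-test, normal data, 30 versus 60.** The true variance of the difference in means is V = σ₁²/30 + σ₂²/60. The pooled test estimates, on average, E = [(29σ₁² + 59σ₂²)/88] × (1/30 + 1/60). The critical value for 88 degrees of freedom is 1.987, so the type I error is roughly the two-sided t tail beyond 1.987/√(V/E).

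| SD, n=30 : n=60 | V | E | V/E | Effective cut-off | Approx. error | Simulated |
|---|---|---|---|---|---|---|
| 1 : 1 | 0.0500 | 0.0500 | 1.00 | 1.987 | 5.0% | 4.8–4.9% |
| 1.5 : 1 | 0.0917 | 0.0706 | 1.30 | 1.744 | 8.5% | 8.3–8.9% |
| 2 : 1 | 0.1500 | 0.0994 | 1.51 | 1.618 | 10.9% | 10.8–11.1% |
| 1 : 1.5 | 0.0708 | 0.0919 | 0.77 | 2.264 | 2.6% | 2.6–2.7% |

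Welch's test in the same settings gives about 5% (4.8 to 5.3% over the simulations). The first row shows that unequal sizes alone leave the error at 5%.

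**Step 4. The whole two-stage rule.** With Mann-Whitney if either group fails the pre-test and pooled t otherwise, at sizes from 15/35 to 30/70:

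- equal SD and shape, normal or lognormal: 4.6 to 5.7%;
- normal data, smaller group's SD 1.5 to 2 times larger: 8.3 to 12.8%;
- normal data, larger group's SD 1.5 to 2 times larger (15/35 and 25/50): 1.4 to 2.8%;
- normal data, balanced 30/30, SD ratio 1 to 2: 4.9 to 5.5%.

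The pre-test thus gives no protection against unequal variances. Skew that it misses does not by itself raise the error when both groups share one distribution.

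**The case against.** The case for leaving the rule alone is substantial.

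- **Unequal sizes are harmless by themselves.** A reader might infer that consecutive recruitment, which need not give equal groups, invalidates the t-test. Step 3 shows that it does not; unequal SDs are needed as well, and the protocol gives none. At milder ratios of 1.1 to 1.2 the error is only 5.7 to 6.6%, or 4.2 to 3.6% when the larger group is the more variable. This stands. The distortion is conditional.
- **Skewed variables are not analysed invalidly.** Detected skew goes to a valid rank test, and undetected skew under a common distribution leaves the t-test near 5%. This also stands. What remains is some inefficiency (under one assumed location shift at log-SD 0.8, Mann-Whitney had 77% power against 71% for t) and an unreliable choice of test.
- **The pre-test may not be weak.** It is tempting to say that it rarely rejects. That holds only for the uncorrected version; with Lilliefors correction, detection at n=30 is about 80% for exponential data.
- **The replacements are imperfect.** With 30 versus 60 and unequal spread, Mann-Whitney drifts to 6.7 to 8.3% on normal data with equal centres and 7.0 to 8.8% on lognormals with equal medians. Welch reaches 5.6 to 11.4% when skew and unequal SDs combine. This is a limit of the remedy, not a defence of the present rule.
- **Test choice per variable is often left to an analysis plan**, and this is a pilot study. However, the protocol does not leave the matter open: it states the summary, the pre-test and the form of the t-test.

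None of this answers the mismatch between mean ± SD and Mann-Whitney, which needs no assumption about sizes or variances.

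**Conclusion.** The point holds, at minor severity. The firm part is the summary: the plan prescribes mean ± SD for variables that it judges non-normal and compares by ranks, which can produce figures such as 1.65 ± 2.16 for a positive quantity. That example assumes a lognormal shape; the mismatch itself is in the text.

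The conditional part is the choice of test. The gate has little power if uncorrected, does not examine variances, and leads by default to a pooled t-test. If sizes and variances both differ, the error is about 8 to 11%, or about 3% in reverse at ratio 1.5, against about 5% for Welch. This rests on an assumed 30 versus 60 split, SD ratios of 1.5 to 2 and normal data.

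The documents do not support a claim that the trial's main conclusion is at risk. The primary endpoint (implantation success, in-hospital complications, 30-day mortality) is categorical and falls under the chi-square or Fisher rule. Only continuous secondary and descriptive variables are affected, and the laboratory values are collected without being named as endpoints.

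**What to change.** Amend the Analysis and Statistics entry in three ways:

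1. Report median (IQR) for every variable compared by Mann-Whitney, keeping mean ± SD for those compared by a t-test.
2. Replace Student's t-test with Welch's t-test.
3. Name the test for each continuous secondary endpoint in advance and drop the Kolmogorov-Smirnov result as the deciding rule. For procedure duration and radiation time, specify a rank test, or an analysis on the log scale with geometric means.

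This takes about two sentences and needs no new data or software. The price is a trivial loss of power if the variances are in fact equal. Where strong skew and unequal spread occur together, neither Welch nor Mann-Whitney fully restores the 5% level, so p-values for such variables should be read with that reservation.

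### NYHA class and MR severity are ordered scales, but the rule that most naturally covers them, chi-square or Fisher, ignores the order and loses power against a consistent shift (minor)

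*Protocol*

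**What the plan says.** The Objectives row of the protocol synopsis sets a safety primary endpoint: "The primary endpoint is related to safety with regard to successful MitraClip® implantation, in-hospital complication rate, and 30-day mortality". Under efficacy it names procedure duration and radiation time first. It then lists as further secondary endpoints "changes in MR and clinical parameters: NYHA class", followed by quality of life, the 6-minute walk test, LV ejection fraction and LV end-diastolic diameter. The Visit Schedule (Table 1) collects NYHA class and transthoracic echocardiography at baseline and at 3 months.

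The Analysis and Statistics row has a two-part rule. Continuous data are "compared with the unpaired student`s t-test or Mann-Whitney U test if not normally distributed". For the rest: "Categorical variables will be evaluated as percentage and compared with the qui-square test or Fisher`s exact test". The threshold is given as "A p-value <0.05 is considered to be significant". No ordinal or trend test is named, and the row does not say which part applies to NYHA class or to MR. The protocol describes MR severity in ordered terms at entry but defines no grading scale.

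The Sample Size row says: "No sample size calculation will be performed because this is an observational pilot study".

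**The concern.** NYHA class is an ordered scale, and so is graded MR. In this row Mann-Whitney is the fallback for continuous data that fail a normality check, and it is not offered for ordered classes. A class summarised as percentages therefore goes most naturally to chi-square or Fisher. Pearson chi-square, and Fisher in its usual form for larger tables, give the same p-value if the class labels are shuffled. A difference between classes I and II counts the same as one between I and IV.

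The study asks whether diabetic patients do worse or as well. That is a directional question about a shift along the scale. An omnibus test spreads such a shift over all its degrees of freedom and is more likely to miss it. At stake is sensitivity on two secondary endpoints, in a single-centre study whose size is set by 12 months of recruitment. Error control is not at stake.

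**Working it through.** **Nothing to reproduce.** The protocol states no sample size, effect or power, so every figure below is an illustration. The significance level of 0.05 comes from the protocol; a two-sided test is assumed, because sidedness is not stated.

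**Step 1: analytic comparison.** Take an effect that a 1-df ordered test detects with 80% power.

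- Noncentrality needed on 1 df: (1.960 + 0.842)² = 7.85.
- Put the same noncentrality into a k-class chi-square, which has k − 1 degrees of freedom when two groups are compared. Power is the probability that a noncentral chi-square variable exceeds the 95th percentile of the central one.
- This assumes that the whole effect lies along the linear trend.

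| Test | df | Power at noncentrality 7.85 | Noncentrality for 80% power | Extra patients for 80% |
|---|---|---|---|---|
| Ordered (1 df) | 1 | 80% | 7.85 | none |
| Chi-square, 3 classes | 2 | 71% | 9.63 | 9.63 / 7.85 = 1.23, so 23% |
| Chi-square, 4 classes | 3 | 64% | 10.90 | 10.90 / 7.85 = 1.39, so 39% |

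The last column holds because noncentrality is proportional to sample size for a fixed effect and allocation.

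**Step 2: simulation of the two tests.** Pearson chi-square was compared with the tie-corrected Mann-Whitney test, with 10,000 runs per setting and a proportional-odds shift between groups. The group sizes (diabetic:non-diabetic), class distributions and odds ratios are all assumed.

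| Class distribution in reference group | Sizes | Odds ratio | Chi-square | Mann-Whitney |
|---|---|---|---|---|
| 15/45/30/10% | 20:40 | 0.4 | 28% | 44% |
| 15/45/30/10% | 30:60 | 0.5 | 25% | 38% |
| 15/45/30/10% | 30:60 | 0.4 | 41% | 59% |
| 15/45/30/10% | 50:100 | 0.4 | 66% | 82% |
| 50/35/10/5% | 30:60 | 0.4 | 45% | 59% |
| 30/50/20% | 30:60 | 0.4 | 47% | 58% |

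Over all settings run, chi-square lost about 5 to 18 percentage points. With no true difference, both tests rejected in about 4 to 5% of runs, so both are valid.

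**Step 3: where the loss disappears or reverses.**

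- If the scale is cut to two levels, chi-square has 2 − 1 = 1 degree of freedom and loses nothing against a rank test on the same two levels.
- For an assumed non-monotone difference (30/20/30/20% against 15/45/30/10%, 30:60), chi-square had 63% power and Mann-Whitney 8%.

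The calculations cover chi-square only. Fisher's exact test ignores order in the same way, but its loss was not computed.

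**The case against.** The strongest reply is that the protocol never assigns NYHA class or MR to the categorical rule. Both endpoints are worded as changes. An analyst could treat a change in class as a number and use the t-test or Mann-Whitney rule, and Mann-Whitney is already in the plan. Assigning tests to individual secondary endpoints is often left to a statistical analysis plan, which is not shown here. This stands in part: the assignment to chi-square or Fisher is the natural reading, not an explicit statement. It does not remove the point, because the protocol itself fixes a two-part rule with no place for ordered data. Where the rule is ambiguous, the test can also be chosen after the data are seen.

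The second reply is that little is lost. Chi-square and Fisher are valid, the percentages shown with the test let a reader see the direction, and a pilot with no power target misses no stated power. All of this stands and keeps the point minor.

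A reader might infer that these are the main clinical efficacy endpoints. The Objectives row does not support that. The primary endpoint is safety, procedure duration and radiation time come first under efficacy, and MR and NYHA class are two of six further secondary endpoints. The other four are measured or scored and fit the continuous rule.

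A reader might also infer that a rank test costs nothing. Step 3 of the working shows otherwise for non-monotone differences.

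**Conclusion.** The point holds, at minor severity. On its natural reading, the Analysis and Statistics row sends two ordered secondary endpoints to tests that are valid but ignore order. Against a consistent shift between diabetic and non-diabetic patients, those tests have less power than a rank test.

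The size is illustrative: 80% falls to about 71% with three classes and 64% with four if the effect is wholly linear, or about 5 to 18 points in the assumed simulation settings. It would be wrong to conclude that this study loses 16 points or needs 39% more patients. The protocol gives no group sizes, effect, class distribution or MR scale, and a two-level cut would bring the loss to zero. The primary safety conclusion is untouched.

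**What to change.** In the Analysis and Statistics row, state that NYHA class and MR grade at 3 months, or their change from baseline, are compared between groups with the tie-corrected Mann-Whitney test. If numbers allow, a proportional-odds model adjusted for baseline class can be named instead. Choose one option, say which variable is analysed and name the MR grading scale before the data are examined. Keep percentages per class as the display, and reserve chi-square and Fisher for nominal and binary variables. If a two-level cut is preferred, specify the cut in advance; chi-square or Fisher is then appropriate.

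The cost is a sentence or two. Mann-Whitney is already in the plan, and the baseline and 3-month assessments are already scheduled, so no extra data are needed. There are two small downsides: a rank test has little power against non-monotone differences, and the proportional-odds model adds an assumption that may be hard to check in a small pilot. Showing the percentages per class lets a reader spot a non-monotone pattern.
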